# The nutrition and immunity (nutrIMM) study: protocol for a non-randomized, four-arm parallel-group, controlled feeding trial investigating immune function in obesity and type 2 diabetes

**DOI:** 10.3389/fnut.2023.1243359

**Published:** 2023-09-01

**Keywords:** immunology, hyperglycemia, nutrition, obesity, type 2 diabetes, insulin resistance, North American diet

## Abstract

**Introduction:**

Individuals with obesity and/or type 2 diabetes are at higher risk of infection and have worse prognoses compared to healthy individuals. Several factors may influence immune responses in this population, including high adiposity, hyperglycemia, and unhealthy dietary habits. However, there is insufficient data on the independent or clustered contribution of these factors to obesity-related immune dysfunction, especially accounting for dietary intake. This study aims to establish the independent contribution of obesity and hyperglycemia to immune dysfunction independent of diet in adults with and without obesity with or without type 2 diabetes.

**Methods:**

The Nutrition and Immunity (nutrIMM) study is a single-centre, non-randomized, four-arm, parallel-group, controlled feeding trial. It will enroll adults without obesity (Lean-NG) and with obesity and three metabolic phenotypes of normoglycemia, glucose intolerance, and type 2 diabetes. Participants will be assigned to one of four groups and will consume a standard North American-type diet for 4 weeks. The primary outcomes are plasma concentration of C-reactive protein and concentration of *ex-vivo* interleukin-2 secreted upon stimulation of T cells with phytohemagglutinin.

**Discussion:**

This will be the first controlled feeding study examining the contribution of obesity, hyperglycemia, and diet on systemic inflammation, immune cell phenotype, and function in adults of both sexes. Results of this clinical trial can ultimately be used to develop personalized dietary strategies to optimize immune function in individuals with obesity with different immune and metabolic profiles.

**Clinical trial registration:**

ClinicalTrials.gov, identifier NCT04291391.

## Introduction

1.

The immune system is a highly complex network that comprises molecules, cells, organs, and tissues, with the primary function of defending the host against pathogens (1). It consists of two major branches: innate and adaptive immunity, which work together to recognize foreign invaders and mount an effective immune response (2). Several factors can affect the resistance of an individual to infection, such as genetics (3, 4), age (5, 6), sex (7, 8), physical activity (9, 10), stress (11, 12), smoking (13, 14), alcohol consumption (15, 16), medications (17, 18), nutrition (19, 20), and obesity (21, 22) as previously reviewed (23).

Obesity is known to cause chronic low-grade systemic inflammation (24), which is characterized by an increased systemic concentration of acute phase proteins and cytokines, including C-reactive protein (CRP), IL-6, IL-18, and TNF-α (25–27). There is an increased release of pro-inflammatory cytokines and chemokines from adipose tissue in the presence of obesity (28, 29). This state leads to excessive recruitment and infiltration of pro-inflammatory immune cells into adipose tissue, such as M1-like polarized macrophages (30), Th1 (31, 32) and Th17 cells (33), and cytotoxic T cells (34), while reducing the number of immune cells that have anti-inflammatory properties, such as T regulatory cells (35, 36). These changes in the immune system can contribute to the development of chronic diseases, including insulin resistance and type 2 diabetes (T2D) (37, 38).

Studies have shown that obesity and T2D are associated with an increased risk of common infections from both bacterial and viral sources (39, 40). However, the mechanisms responsible for this increased risk are not fully understood. Previous research has focused on alterations in the immune system mediated by adipose tissue in obesity and/or T2D, rather than on immune function (41, 42). Recently, it was discovered that T2D is associated with additional perturbations in immune function, independent of obesity status (43). Obese individuals with T2D exhibit impaired neutrophil function and T cell response upon stimulation compared to BMI-matched normoglycemic (NG) obese individuals, despite having more activated Th cells. However, further studies are needed to determine whether the immune function of the Obese-NG group is comparable to that of lean control healthy subjects (43).

Acute inflammatory responses to dietary challenges, such as the oral glucose tolerance test (OGTT), have been proposed as a sensitive indicator of the impact of glycemia on immune responses (23, 27, 44). The OGTT induces a rise in glucose, insulin, and a transient inflammatory response (45–50), which tends to be stronger and more extended in individuals with obese and T2D (51, 52). *In vivo* studies have demonstrated that hyperglycemia increases the expression of pro-inflammatory cytokines, such as TNF-α and IL-1β, by leukocytes (53). Furthermore, after an OGTT, T2D patients had an increased proportion of neutrophils and monocytes over time compared to healthy controls, and the monocyte-AUC correlated positively with the glucose-AUC (54). These findings suggest that glycemia plays a role in immune activation, and further investigation is needed to understand the impact of glycemia on immune responses in individuals with obesity.

Nutrition plays a crucial role in the prevention and treatment of health conditions that have an inflammatory component, such as obesity (55, 56). Saturated fatty acids (SFA) have been shown to have pro-inflammatory properties, while fiber, antioxidants, vitamins, and polyunsaturated fatty acids (PUFA), especially eicosapentaenoic acid (EPA) and docosahexaenoic acid (DHA), generally exert anti-inflammatory and/or immunosuppressive effects in the presence of chronic inflammation as previously reviewed (20). Choline is another nutrient that has been shown to be essential for optimal immune function (57), improving the T cell response to immune challenges by increasing IL-2 secretion (58, 59). These findings suggest that specific nutrients in the diet could have a beneficial effect on immune function, particularly in the context of obesity.

Despite the association between obesity, hyperglycemia/T2D, elevated systemic inflammation, and impaired immune cell response, it remains unclear whether these abnormalities are caused by excess adiposity, dysglycemia, or poor food habits associated with obesity. To dissect the impact of excess body fat and glycemia on immune function, it is crucial to account for food intake by performing controlled feeding studies in humans. Therefore, a comprehensive analysis of systemic inflammation and immune function in healthy lean individuals (Lean-NG), individuals with obesity and normoglycemia (Obese-NG), glucose intolerance (Obese-GI) or T2D (Obese-T2D) is required to understand the independent contribution of excess body fat and glycemia on immune function.

## Methods

2.

### Study objectives and hypothesis

2.1.

The study objectives are:

To establish the independent contribution of obesity and glycemia, independent of diet, on systemic inflammation and immune function outcomes. We hypothesize that systemic inflammation will increase and T cell function, characterized by *ex vivo* IL-2 secretion upon phytohemagglutinin (PHA) stimulation, will decrease progressively from the Lean-NG to Obese-T2D group.To determine the role of glycemia on postprandial inflammatory and immune responses using an OGTT. We hypothesize that a higher glucose AUC will be associated with increased inflammatory responses, a higher proportion of activation markers expressed on immune cells, and a lower proliferation rate by PBMC upon stimulation with anti-CD3/CD28 in Lean-NG, Obese-NG, Obese-GI, and Obese-T2D individuals.To explore the relationship between diet, metabolism, and immune function. We hypothesize that a higher habitual consumption of DHA and choline and lower consumption of SFA, will be associated with enhanced immune function and lower levels of systemic inflammation. Specifically, a higher proportion of DHA in the membranes of RBC will be associated with improved Th1 response (i.e., IFN-γ and TNF-α), despite similar production of IL-2 upon immune challenge, whereas systemic inflammatory markers will be lower. Higher consumption of choline in the form of phosphatidylcholine will improve IL-2 production upon T cell stimulation. Other dietary components (e.g., fiber, antioxidants, and vitamins) will be associated with enhanced immune function in individuals with and without obesity with varying levels of glycemia.

### Outcomes

2.2.

The primary outcomes of this study are the concentration of IL-2 in the supernatant of *ex vivo* stimulated cells, which is a surrogate marker of T cell proliferation, and circulating concentrations of CRP.

### Study design

2.3.

The NutrIMM study is a prospective, non-randomized, four-arm, parallel-group, unicentre, controlled-feeding trial conducted at the Human Nutrition Research Unit (HNRU), University of Alberta (Edmonton, AB, Canada). A total of one-hundred and twenty-eight participants aged between 18 and 70 years will be assigned with a 1:1 male to female ratio to one of four groups (*n* = 32 per group): Lean-NG, Obese-NG, Obese-GI, Obese-T2D. All participants will be followed up for a total of 4 weeks from the date of group allocation. It will not be possible to blind participants or researchers due to the inclusion specifications of the groups. An overview of the study design is shown in Figure 1.

**Figure 1 fig1:**
[figure not shown]
Overview of study design. FFQ, food frequency questionnaire and DXA, dual-energy X-ray absorptiometry.

### Ethical aspects

2.4.

The research protocol was approved by the University of Alberta Ethics Board (Pro00085839) and follows the standards proposed by the Canadian Tri-Council Policy statement on the use of human participants in research. This protocol was developed according to the Standard Protocol Items: Recommendation for Interventional Trials (SPIRIT) (60) and the Template for Intervention Description and Replication (TIDieR) (61). All participants will sign an informed consent document approved by the Human Research Ethics Board of the University of Alberta for study participation and to optionally provide stool samples for a sub-study to investigate the role of gut microbiota on immune function (Supplementary File 1). Participants will sign an additional consent form to select if they allow their biological specimens to be stored for up to 20 years for use in ancillary studies.

### Recruitment and enrolment of participants

2.5.

#### Recruitment

2.5.1.

The trial will recruit males and females from the Edmonton Metropolitan Region via the traditional media (newspaper, radio, and TV), word of mouth, institutional websites, social media advertisements, and posters placed on notice boards at the University of Alberta, obesity clinics, and other facilities from the surrounding area of Edmonton. A website and social media accounts (Instagram and Facebook) with the study information were also developed to support recruitment.^1^ Individuals can be included in the study if they meet all inclusion criteria and no exclusion criteria. All participants will be matched by age and sex, if possible, and participants with obesity will be matched for BMI and/or waist circumference. All females in reproductive stage which are not using contraceptive methods will be tested during the same follicular phase of their menstrual cycle (day 2 to 9), to account for immunometabolic changes, considering 4 weeks the mean duration of a menstrual cycle (62, 63). Participants will be allocated to one of four groups according to specific criteria for BMI, waist circumference, blood pressure, fasting glucose, hemoglobin A1c (HbA1c), triglycerides, and high-density lipoprotein-cholesterol (HDL-C) (Table 1). The cut off points used to identify obesity, cardiometabolic risk factors, and T2D were based on the World Health Organization (64), National Cholesterol Education Program-Adults Treatment Panel III criteria for metabolic syndrome (65) and Diabetes Canada (66), respectively.

**Table 1 tab1:** Eligibility criteria per group of adults.

Criteria	Lean-NG	Obese-NG	Obese-GI	Obese-T2D
BMI (kg/m^2^)	18.5–24.9 (±0.5)	≥ 30 (±0.5)		
Waist circumference (cm)	Males <102; Females <88	Males ≥102; Females ≥88		
Fasting blood glucose (mmol/L)^a^	<5.6		5.6–6.9	≥ 7.0
HbA1c (%)	<5.5		5.5–6.4	≥ 6.5^b^
BP (SBP/DBP, mmHg)	<130/85		NR	
Triglycerides (mmol/L)	<1.7		NR	
HDL-C (mmol/L)	Males ≥1.03; Females ≥1.29		NR	

BMI, body mass index; BP, blood pressure; DBP, diastolic blood pressure; HbA1c, glycated hemoglobin; HDL-C, high density lipoprotein-cholesterol; NR, not required in it that could be normal or elevated; SBP, systolic blood pressure; T2D, type 2 diabetes.

a If participants are at the upper or lower limits for fasting glucose, HbA1c will be used for group allocation.

b Or diagnosis of type 2 diabetes and use of medication.

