### Statistical analysis

2.10.

Continuous variables characterizing each study group will be reported as means with standard deviations or medians with interquartile ranges. Categorical variables will be represented as frequencies and proportions. Data will be checked for normality using the Shapiro–Wilk test, and logarithmic transformation will be employed for variables not normally distributed. The main comparisons in this study will be (1) between groups at each time point using analysis of variance with groups as the main effect followed by a multiple-comparison *post hoc* test and (2) within groups using paired *T*-test to assess differences between time points (i.e., baseline vs. post-intervention). Correlation analysis and linear regression models will be performed to verify the associations between outcomes (e.g., immune cell phenotypes and function, and systemic inflammation) and exposure (e.g., dietary intake or metabolic parameters, such as glucose, insulin, HOMA-IR, and HbA1c) variables. Mixed model repeated measures will be used to analyze variables of the OGTT to assess the effects of time, group, and time*group interaction. Overall comparisons of postprandial responses among groups will be determined using the incremental AUC with the trapezoid method. The statistical analyses will be adjusted for potential confounders and their interaction with the main group effect in cases where groups are unbalanced regarding factors such as physical activity level, use of medication (e.g., anti-diabetic drugs), and BMI, sex, and age if groups are not matched as initially planned. Sensitivity analyses will be conducted to verify the effect sizes of the primary outcomes of the study to assess the power and validity of our results. Comparative analyses using pertinent variables (e.g., age, sex, diet, metabolic profile, primary outcomes) will be performed between participants that completed the study with those who did not (i.e., participant dropouts or discontinuers). A *p*-value <0.05 will be considered to be statistically significant. A detailed analysis plan will be developed before the final analysis with a biostatistician.

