## Discussion

3.

Obesity and T2D are associated with an increased risk of infections and a worse prognosis. Immune dysfunction in these conditions may be caused by abnormalities such as excess visceral adiposity (86), hyperglycemia (87), and unhealthy dietary habits (88). However, there is a lack of clinical trials that have controlled for diet and investigated immune function outcomes in males and females with obesity across different metabolic phenotypes.

To address this gap, the NutrIMM study aims to identify immune markers that are impaired in different health conditions, independent of the effect of diet. This study will also explore the relationship between dietary components, biological sex, and immune function. By understanding these differences, we hope to identify targeted and personalized approaches to improve immunity based on sex and metabolic phenotype.

Our investigation may also lead to the identification of circulating inflammatory markers that predict a lower immune function in individuals with obesity and T2D. This is important for diagnostic purposes as common techniques used to assess immune function are not practical for routine diagnosis. Moreover, our study may identify key nutrients that could improve immune function and guide future targeted and personalized interventions for subsequent trials.

The NutrIMM study is the first to determine the independent contribution of diet, sex, excess body fat, and altered glucose levels on inflammation and immune dysfunction associated with obesity. Other strengths of our protocol include assessing immune function outcomes under controlled feeding conditions, which provides valuable information about the effects of different foods, nutrients, and dietary patterns on health outcomes. This type of study allows for careful monitoring and manipulation of food intake, direct measures of physiological responses to different foods and nutrients, and the development of personalized nutrition recommendations based on an individual’s unique physiological response (89–91).

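### Table 1 requires normal blood pressure, triglycerides and HDL-C in the normoglycemic groups only, so Obese-NG versus Obese-GI or Obese-T2D does not isolate glycemia

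*Protocol article*

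**What the plan says.** Section 2.1 of the protocol article gives the first objective: "To establish the independent contribution of obesity and glycemia, independent of diet, on systemic inflammation and immune function outcomes". The abstract describes the obese participants by glycemia alone, "with obesity and three metabolic phenotypes of normoglycemia, glucose intolerance, and type 2 diabetes". The Discussion (section 3) claims priority for this trial in establishing one thing: "independent contribution of diet, sex, excess body fat, and altered glucose levels on inflammation and immune dysfunction associated with obesity".

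Group membership rests on more than glycemia. Section 2.5.1 says: "Participants will be allocated to one of four groups according to specific criteria for BMI, waist circumference, blood pressure, fasting glucose, hemoglobin A1c (HbA1c), triglycerides". HDL-C completes that list. In Table 1 the limits for blood pressure (<130/85 mmHg), triglycerides (<1.7 mmol/L) and HDL-C ("Males ≥1.03; Females ≥1.29", in mmol/L) cover Lean-NG and Obese-NG. The entry for Obese-GI and Obese-T2D is NR, explained in the footnote as "NR, not required in it that could be normal or elevated".

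On balancing the groups, section 2.5.1 says: "All participants will be matched by age and sex, if possible, and participants with obesity will be matched for BMI and/or waist circumference". Section 2.10 adjusts for confounders only when the groups turn out unbalanced, and it gives its factors as examples, not as a closed list.

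**The concern.** An obese person with normal glucose and HbA1c but triglycerides of 2.0 mmol/L does not qualify for Obese-NG. With fasting glucose of 5.8 mmol/L and HbA1c of 5.8%, the same person qualifies for Obese-GI with those triglycerides. The rule thus removes hypertension and dyslipidemia from the normoglycemic side of the comparison and leaves them on the dysglycemic side.

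A difference in CRP or in IL-2 secretion between Obese-NG and Obese-T2D could then come from glycemia, from the accompanying cardiometabolic abnormalities, or from both. Section 2.11 bases the sample size on this same contrast. Reporting the difference as the independent contribution of glycemia would claim more than the comparison can show.

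**Working it through.** **Reading the table.** Each limit fills the two normoglycemic columns and NR fills the other two. The fasting glucose row uses the same merged layout, with <5.6 covering both normoglycemic groups. The text of section 2.5.1 confirms that these variables decide allocation, so the asymmetry does not come from how the table was extracted.

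**Effect on each contrast.**

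| Contrast | Rule for BP, triglycerides, HDL-C | Consequence |
|---|---|---|
| Lean-NG vs Obese-NG | same limits on both sides | balanced; scope limited to normal measured values |
| Obese-NG vs Obese-GI | limits vs none | differs by rule beyond glycemia |
| Obese-NG vs Obese-T2D | limits vs none | differs by rule beyond glycemia |
| Obese-GI vs Obese-T2D | none on either side | not affected by the unequal rule |

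**Is it handled elsewhere?** Matching covers age, sex, and BMI and/or waist. The adjustment factors named in section 2.10 are physical activity, medication, BMI, sex and age. Blood pressure, triglycerides and HDL-C appear in neither, although the list in section 2.10 is open-ended. The limitations in section 3 do not mention the point.

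**The plan's own figure, used only for scale.** Section 2.11 states power of 0.81 (written there as β) with 32 per group and an effect size of 30%. Reading 30% as Cohen's f = 0.30 in a four-group ANOVA gives noncentrality 0.30² × 128 = 11.52 on 3 and 124 degrees of freedom, and power of 0.810, which matches. If the four means are equally spaced (an assumption), step × √1.25 = 0.30, so the step is 0.268 SD and the two steps from Obese-NG to Obese-T2D are 0.537 SD.

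**Possible size of the distortion.** None of these inputs is in the documents. Let p be the share of Obese-T2D with an abnormal value (0 in Obese-NG by rule), d the shift in the outcome in SD that goes with it, and the true glycemia effect zero. The spurious difference is p × d. The last column is the rejection rate of a nominal two-sided 5% t-test with 32 per group, from 20,000 simulated trials per row.

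| p | d | p × d (SD) | rejection rate |
|---|---|---|---|
| 0.3 | 0.3 | 0.09 | 6.5% |
| 0.5 | 0.5 | 0.25 | 16% |
| 0.7 | 0.5 | 0.35 | 27% |
| 0.9 | 0.8 | 0.72 | 80% |

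The result runs from almost no distortion to a difference larger than the 0.537 SD benchmark. The documents do not say where the trial falls in that range, and CRP and IL-2 need not fall in the same place.

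**What a restricted comparison could show.** Suppose 50–90% of a dysglycemic group has an abnormal value (again an assumption). Those meeting the Obese-NG limits then number 32 × 0.5 = 16 down to 32 × 0.1 ≈ 3. Against 32 Obese-NG, a two-sided t-test for 0.537 SD has power of about 40% with 16 and 14% with 3. The 95% half-width, t × √(1/n + 1/32), is about 0.6 SD and 1.2 SD respectively.

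**The case against.** The strongest reply is that this is a disclosed design choice. The article calls the groups metabolic phenotypes and lists blood pressure and lipids as allocation criteria. NR permits abnormal values but does not require them. The adjustment list in section 2.10 is open, the variables are measured, and a detailed analysis plan is still to be written. Glycemia is also studied by regression on glucose, insulin, HOMA-IR and HbA1c, and through the OGTT. All of this stands. It rules out saying that adjustment is excluded, or that the trial can learn nothing about glycemia. The claim attached to the group contrast is not rescued by it. The eligibility rule sits in the protocol, and no Obese-NG participant can qualify with measured values beyond the cut-offs, so adjustment in that contrast relies on extrapolation.

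A second reply is that hypertension and dyslipidemia may partly follow from dysglycemia. If so, the contrast measures dysglycemia together with what accompanies it, which is a legitimate target but not the stated one.

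A reader might also infer that the obesity effect is biased toward zero, so that the design overstates glycemia and understates obesity at once. The documents do not support this. Lean-NG and Obese-NG carry identical limits, and holding those factors equal arguably serves the aim of isolating obesity. What remains is a question of scope.

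**Conclusion.** The point holds for Obese-NG versus Obese-GI and Obese-NG versus Obese-T2D. As Table 1 is written, these comparisons differ by rule in permitted hypertension and dyslipidemia, and they do not isolate glycemia. This rests only on Table 1 and the stated objective.

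The magnitude is unknown, and the figures above only illustrate it. Even the value of zero in Obese-NG applies to measured values only: section 2.7.1 lets participants stay on lipid-lowering and blood-pressure-lowering drugs, and Table 1 does not say whether a treated normal value qualifies. Lean-NG versus Obese-NG needs a narrower label, and Obese-GI versus Obese-T2D needs no change on this account.

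**What to change.** 1. In sections 2.1 and 3, describe Obese-NG versus Obese-GI and Obese-T2D as the effect of dysglycemia together with its accompanying cardiometabolic abnormalities. Describe Lean-NG versus Obese-NG as obesity with normal glycemia, blood pressure and lipids. List the unequal criteria among the limitations.
2. In the analysis plan still to be written, pre-specify two supportive sensitivity analyses for CRP and IL-2, reported as estimates with confidence intervals:
   - (a) the contrasts of Obese-NG with Obese-GI and with Obese-T2D, keeping only those Obese-GI and Obese-T2D participants who meet the Obese-NG limits for blood pressure, triglycerides and HDL-C;
   - (b) regression on the glycemia measures adjusted for these three values, including a version within Obese-GI plus Obese-T2D, where the eligibility rule is the same.
3. State in advance that agreement with (a) does not by itself restore a claim of independent glycemia effects, because (a) may be too imprecise to contradict anything.

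Changing eligibility is not proposed. The trial status section expected recruitment to finish in July 2023, so it would probably come too late.

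The cost is wording and two analyses of variables already collected. The drawbacks are a narrower claim, a possibly very small subset in (a), and the risk in (b) of adjusting away effects that run through blood pressure or lipids.
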